#### Secondary objectives

Secondary objectives are to assess safety of DCBI therapy after CRS-HIPEC and determine whether a specific immunological response occurs due to dendritic cell vaccination.

#### Safety

Previous clinical studies have shown that injection with tumour lysate-pulsed autologous DCs was overall well tolerated without systemic toxicity, with the exception of low-grade flu-like symptoms like fever and rigours. No grade 3 or 4 toxicity was observed.^11^ However, safety and tolerability after major surgery has yet to be determined.

The administration of autologous cells that have been loaded with allogeneic human materials is a potential health risk. Because not the lysate itself is administered to the patients, but only after it has been processed by autologous dendritic cells, risks are expected to be limited.

The necessary sample size for the detection of grade 3 toxicity is calculated to be 20 patients (figure 3). All adverse events, serious adverse events and suspected unexpected serious adverse reactions will be monitored and reported by the sponsor.

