**Figure 3 F3:**
[figure not shown]
Sample size calculation: Assuming the sensitivity for detecting grade 3 (or higher) toxicity is 99%. Expected prevalence of grade 3 toxicity in the study population is 2.5%.

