
### Statistical analysis

The statistical analyses/data summaries will be performed using SPSS. Other tools may be used for exploratory summaries and graphical presentations.

Primary endpoint is to determine the feasibility of administering DCBI after CRS-HIPEC in patients with malignant peritoneal mesothelioma. Based on previous results it is known that from all patients with colorectal carcinoma that underwent CRS-HIPEC, about 25% is not able to receive adjuvant systemic therapy due to postoperative complications. Feasibility is set if 15 of 20 patients (75%) were able to undergo leukapheresis successfully, production of PheraLys and dendritic cell vaccines was successful and when patients were able to complete the full adjuvant treatment schedule.

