Currently, CRS-HIPEC is the gold standard for a selected group of patients suffering from MPM. Eligibility for CRS-HIPEC is dependent on several clinical aspects such as ‘peritoneal carcinoma index’ (PCI), histological subtype and overall patient health condition. Previous studies have shown that outcome after CRS-HIPEC strongly depends on the completeness of cytoreduction.^1^ Unfortunately it is very difficult to achieve complete cytoreduction in patients with high PCI score. It has been reported by others that immunotherapy is possibly more effective in patients with low tumour load. Therefore, in this study DCBI is given as adjuvant treatment after CRS-HIPEC. However, if a significant clinical effect can be achieved, in the future DCBI might be used as a neoadjuvant therapy making CRS-HIPEC with complete cytoreduction available for a larger number of patients.

We acknowledge the fact that this study has limitations. One limitation of this study is the small number of patients that will be included. Given the rarity of MPM, it is difficult to include large numbers of patients. However the sample size of this current study, should be sufficient to determine the feasibility and safety of adjuvant DCBI after CRS-HIPEC.

Another limitation of this study design is that it is not possible to determine radiological response to DCBI treatment. After debulking surgery, MPM will not be detectable on CAT scans. Therefore the response to DCBI treatment must be determined by assessing the immune response and overall clinical condition of each patient. Clinical effect of DCBI on overall survival can only be determined after a longer period of follow-up.

If DCBI is considered feasible as adjuvant treatment for MPM, a larger phase III clinical trial should be conducted to determine the effect on surgical and oncological outcome. Because MPM incidence in the Netherlands alone is very low, this clinical trial would have to be conducted internationally.

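### Twenty patients give only about a 40% chance of seeing a grade 3 toxicity at the expected 2.5% rate, so the claims that this size detects such toxicity and is sufficient for safety are not supported

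*Protocol article*

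**What the plan says.** Safety is a secondary objective, and the Safety section gives it a sample size: "The necessary sample size for the detection of grade 3 toxicity is calculated to be 20 patients", with a reference to Figure 3. The caption of that figure supplies two inputs: "Assuming the sensitivity for detecting grade 3 (or higher) toxicity is 99%. Expected prevalence of grade 3 toxicity in the study population is 2.5" (the last figure is also a percentage). No confidence level, target precision or alternative event rate is given in the text.

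The Discussion, after acknowledging that the trial is small and the disease rare, says that the sample size "should be sufficient to determine the feasibility and safety of adjuvant DCBI after CRS-HIPEC".

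Two statements under Statistical analysis bear on how many patients will be exposed. The feasibility rule begins "Feasibility is set if 15 of 20 patients (75%) were able to undergo leukapheresis successfully" and goes on to require completion of the full schedule. Its background is colorectal experience with CRS-HIPEC, in which "about 25% is not able to receive adjuvant systemic therapy due to postoperative complications".

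**The concern.** An event expected in 2.5% of patients yields half a case on average in 20 patients. A sample in which the expected count is below one cannot be relied on to show the event at all, so it is hard to see how 20 was obtained as the number needed to detect it, or how it could settle safety.

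This matters beyond one sentence. It is the only sample size calculation the article offers for the 20 patients; feasibility has a cut-off but no derivation. Safety is also one of the two conditions for going on to phase III, both in the strengths and limitations list and at the end of the Introduction. The Safety section itself says that tolerability after major surgery has still to be established. A reader planning the next trial could therefore take more reassurance from this one than 20 patients can give.

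**Working it through.** **Inputs**
- n = 20 (Safety section; target sample size in Table 1).
- Expected prevalence p = 0.025 and assumed sensitivity Se = 0.99 (Figure 3 caption).
- 15 exposed, used only as a lower scenario. If the 25% that the Statistical analysis section cites never started treatment, 0.75 × 20 = 15 would be exposed.

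**Step 1. Can 20 be reproduced?**

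*99% as the chance of at least one case.* Solve 1 − (1 − p)^n = 0.99:
- n = ln(0.01)/ln(0.975) = 181.9, so 182.
- With 99% per-case sensitivity as well, p becomes 0.99 × 0.025 = 0.02475, and n = ln(0.01)/ln(0.97525) = 183.8, so 184.
- Lower detection targets at p = 0.025 also fail: 64 for 80%, 91 for 90%, 119 for 95%.

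*Injections as the unit.* Each patient is scheduled for five. Treating 100 injections as independent gives 1 − 0.975^100 = 92.0%, and 99% would need 37 patients. The caption in any case gives a prevalence in the study population, not per injection.

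*Precision of the estimated sensitivity.* The usual formula is n = z² × Se(1 − Se)/(d² × p). At n = 20 and two-sided 95% confidence, the half-width d is 1.96 × √(0.99 × 0.01/(20 × 0.025)) = 0.276, or 27.6 points.

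*Precision of the estimated prevalence.* n = 1.96² × 0.025 × 0.975/d². With d = 0.07 this is 19.1, so 20. Allowing for 99% sensitivity (and perfect specificity), n = 1.96² × 0.02475 × 0.97525/(0.99² × 0.07²) = 19.3, again 20. The half-width of 7 points is an assumption that stands nowhere in the text. In the simpler formula, 6 points gives 27 and 8 points gives 15.

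So 20 does not follow from the two stated inputs alone. It can be reached by adding a third, unstated one.

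**Step 2. What 20 patients deliver at 2.5%**

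| Exposed | Expected cases | P(at least one) = 1 − 0.975^n | Same, with 99% per-case sensitivity |
|---|---|---|---|
| 20 | 20 × 0.025 = 0.5 | 39.7% | 39.4% |
| 15 | 15 × 0.025 = 0.375 | 31.6% | 31.3% |

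**Step 3. What rates 20 patients can reveal or exclude**
- 99% chance of at least one case: rate of 1 − 0.01^(1/20) = 20.6% or more.
- 95% chance: rate of 1 − 0.05^(1/20) = 13.9% or more.
- Zero events, exact one-sided 95% upper limit: 13.9% with 20 exposed; 1 − 0.05^(1/15) = 18.1% with 15.

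**The case against.** The best defence is that the caption offers 99% as an assumed sensitivity and not as a promised probability that the trial will see a case. A reader might infer that the protocol claims 99% detection at a 2.5% rate and that 20 should have been 182. The document does not say so. The figure of 182 holds only if 99% has that meaning, and the formula sits in a figure that is not available here. As shown above, a precision calculation with an undisclosed half-width of about 7 points would give 20. This part stands: a plain arithmetic error cannot be asserted. It does not rescue the detection claim, because under the per-case reading the chance of seeing a case is still 39.4%. Nor would a half-width of 7 points around 2.5% justify calling the sample sufficient for safety.

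Second, 15 is the threshold for completing the full schedule. A patient who stops after one vaccination has been exposed, so 15 completers do not mean 15 exposed. That also stands. The 15-patient figures are a conditional scenario, supported only by analogy with systemic therapy in colorectal patients.

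Third, a reader might infer that zero grade 3 events would be taken as proof of safety. No section says this, and adverse events are to be monitored and reported, with a yearly safety report. Nor is zero the likeliest outcome at clearly higher rates: with 20 patients it is the single most likely count only below 1/21, about 4.8%. At 5%, one event (37.7%) is already likelier than none (35.8%).

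Last, safety is secondary, the 15-of-20 feasibility decision is untouched, and the small size is acknowledged and justified by rarity. That argues for keeping 20 patients, not for keeping a claim that they do not support.

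**Conclusion.** The point holds in a limited form. The stated size cannot be reproduced from the two visible inputs. Under either meaning of the 99%, 20 exposed patients give only about a 40% chance of seeing a grade 3 or higher toxicity that occurs at the expected 2.5% rate, and about 32% if as few as 15 are exposed. If 99% is meant as the chance of at least one case, the shortfall is 20 against 182. Zero events among 20 would still leave rates of up to 13.9% compatible with the data (one-sided 95%), more than five times the expected rate (13.9/2.5 = 5.6). The Discussion's statement on safety therefore goes beyond the design.

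The calculation assumes independent patients with a common event rate and takes the caption's 2.5% at face value. It does not depend on what Figure 3 contains, except for the figure of 182.

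**What to change.** Keep the 20 patients and change the claims:

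1. State the formula and all inputs behind Figure 3, including any precision or confidence level and what the 99% refers to; or withdraw the detection claim.
2. In its place, say what the design delivers, for example: *With 20 exposed patients, the chance of observing at least one grade 3 or higher toxicity is about 40% if the true rate is 2.5%, and zero events would exclude rates above 13.9% (one-sided 95%). With 15 exposed, these figures are 32% and 18.1%.*
3. Report the observed grade 3 or higher rate with its exact upper confidence limit.
4. Remove from the Discussion the statement that the sample size is sufficient to determine safety.

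The exact safety denominator and the date from which toxicity is counted may be left to the full protocol or SAP, and nothing is asked about them here. The cost is wording in the Safety section, the Figure 3 caption and the Discussion, one reported limit, and a safety claim that reads less favourably. No patients are added, and the feasibility rule does not change.

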**Figure 3 F3:**
[figure not shown]
Sample size calculation: Assuming the sensitivity for detecting grade 3 (or higher) toxicity is 99%. Expected prevalence of grade 3 toxicity in the study population is 2.5%.

#### Immune response

Assessment of immune responses will be conducted on three levels in all treated patients; (1) responses that mark successful vaccination, (2) enhanced frequencies of tumor-specific T cells in peripheral blood samples and (3) frequency shifts in other immune cell subsets.Keyhole limpet hemocyanin (KLH) is added to the vaccines as a surrogate marker. With the use of KLH, we will assess whether an immune response against the vaccine has occurred and whether this response persists. KLH is known to induce a specific adaptive immune response readily detectable in sera (antibody response) and skin tests (cellular response) of vaccinated individuals. Serum samples will be collected before, during and after DCBI as well as at selected intervals during follow-up. Humoral responses to KLH will be detected using ELISA. Furthermore, patients will undergo a DTH skin test before and after DCBI. DTH responses will be evaluated for local inflammation after 48 hours and 3 mm punch biopsies will be collected in case inflammation occurs. These biopsies will subsequently be used for in situ immunostainings of DC, myeloid derived suppressor cells (MDSC), and CD8 +T cells.To assess vaccine-induced frequencies of tumor-specific T cells, we will conduct a potency assay in accordance with the ‘Guideline on potency testing of cell based immunotherapy medicinal products for the treatment of cancer’ as provided by the European Medicine Agency (EMA) in 2016 (EMA/CHMP/BWP/271475/2006 rev.1). The proposed assay can shortly be described as a co-culture of T cells isolated from pre- and post-treatment peripheral blood samples with autologous DCs loaded with autologous tumour lysate. Subsequently, we will measure T cell proliferation and activation markers via multicolour flow cytometry.Phenotypical analysis of immune cell subsets will be conducted using flow cytometry to detect vaccine-induced changes in the frequencies of >100 immune cell (subsets) that represent distinct lineages and/or express different levels of activation, differentiation and co-signalling markers. Staining of fresh patient material at different time points will allow enumeration of different immune cells throughout therapy. Subsequent bulk analysis of frozen material focusses solely on an extensive array of T cell, MDSC and DC markers. Combination of these readouts allows for the generation of immune profiles for individual patients. The analysis of these profiles in turn will allow for the determination of prospective markers and better stratification of patient populations suited for vaccination therapy.

### Statistical analysis

The statistical analyses/data summaries will be performed using SPSS. Other tools may be used for exploratory summaries and graphical presentations.

Primary endpoint is to determine the feasibility of administering DCBI after CRS-HIPEC in patients with malignant peritoneal mesothelioma. Based on previous results it is known that from all patients with colorectal carcinoma that underwent CRS-HIPEC, about 25% is not able to receive adjuvant systemic therapy due to postoperative complications. Feasibility is set if 15 of 20 patients (75%) were able to undergo leukapheresis successfully, production of PheraLys and dendritic cell vaccines was successful and when patients were able to complete the full adjuvant treatment schedule.

### Patient and public involvement

The Dutch patient association for patients with mesothelioma ‘Instituut Asbestslachtoffers’ and the Erasmus MC, Rotterdam, have worked together closely for years on the development of dendritic cell immunotherapy for mesothelioma. The patient association has received a copy of the study protocol to comment on the research question and outcome measures and also received the patient information folder to comment on patients preference and clarity of the information folder. During the study, feedback is provided on the inclusion rate and patient experiences. The results of the study will also be communicated to the patient association, which can then distribute them among their members.

## Ethics and dissemination

The study will be conducted in compliance with the ‘Medical Research Involving Human Subjects Act’ (WMO) and according to the principles of the Declaration of Helsinki (64th World Medical Association General Assembly, Fortaleza, Brazil, October 2013).

If protocol modifications occur, the new protocol has to be approved by the Central Committee on Research Involving Human Subjects and the Research Ethics Committee of the Erasmus MC before they can be implemented. Data collection, data assessment and data analysis will be performed according to the local guidelines for data management of the Erasmus MC.

To generate more awareness for this current study and to increase referrals of potential study candidates to the Erasmus MC, a short Dutch summary of the study will be submitted to The Dutch Journal for Oncology (NTVO in Dutch). Also, presentations about the study have been given at the Dutch Society of Surgery meeting and the Peritoneal Surface Oncology Group International meeting in Paris.

The results of this clinical trial will be submitted for publication in a peer-reviewed scientific journal.

The investigator will permit auditors to carry out site visits to audit the compliance with regulatory guidelines. Similar auditing procedures may be conducted by agents of any regulatory body reviewing the results of this study.

The sponsor will submit a yearly safety report to the accredited METC, competent authority and competent authorities of the concerned Member States. This safety report consists of; 1 a list of all suspected (unexpected or expected) serious adverse reactions, 2 a report concerning the safety of the subjects consisting of a complete safety analysis and an evaluation of the balance between the efficacy and the harmfulness of the medicine under investigation.

Within 1 year after the end of the study, the investigator/sponsor will submit a final study report with the results of the study, including any publications/abstracts of the study, to the accredited METC and the Competent Authority.

Currently three patients are included in the study protocol. The final patient is expected to be included at the end of 2020. First results are expected in 2021.

## Discussion

The main objective of the MESOPEC trial is to determine feasibility of DCBI as adjuvant treatment after CRS-HIPEC in patients with MPM. Secondary objectives are to assess safety and to monitor the immune response after DCBI. The MESOPEC trial is the first clinical trial offering adjuvant dendritic cell immunotherapy to patients with MPM. So far (neo)adjuvant systemic chemotherapy has shown no benefit on surgical or oncological outcome for MPM.^14^ Systemic chemotherapy, using cisplatin and pemetrexed, is standard treatment in pleural mesothelioma and has been applied to patients with peritoneal mesothelioma. This has shown limited efficacy, considerable toxicity and even mortality, making it unfit for the treatment of MPM.^15^

The DCBI used in this current trial consists of personalised dendritic cell vaccines, produced with autologous dendritic cells that are loaded with tumour associated antigens derived from allogeneic tumour cell lysate. This treatment approach has multiple advantages. The biggest advantage of this strategy is that it is possible to produce personalised anti-cancer vaccines on a scale sufficient for clinical implementation in larger groups of patients. Another advantage is that so far DCBI has shown no severe side effects and therefore causes little morbidity especially when compared with current other adjuvant treatment options, like systemic chemotherapy.

Analyses of tissue and blood samples that are collected throughout the study will provide valuable information for scientists and clinicians regarding the immunologic response after DCBI. Furthermore, potential of DCBI can be tested in vitro by culturing tumour cell lines derived from tumour tissue obtained during CRS. By doing so, in the future, patients that will respond to immunotherapy can be identified before starting treatment.

Currently, CRS-HIPEC is the gold standard for a selected group of patients suffering from MPM. Eligibility for CRS-HIPEC is dependent on several clinical aspects such as ‘peritoneal carcinoma index’ (PCI), histological subtype and overall patient health condition. Previous studies have shown that outcome after CRS-HIPEC strongly depends on the completeness of cytoreduction.^1^ Unfortunately it is very difficult to achieve complete cytoreduction in patients with high PCI score. It has been reported by others that immunotherapy is possibly more effective in patients with low tumour load. Therefore, in this study DCBI is given as adjuvant treatment after CRS-HIPEC. However, if a significant clinical effect can be achieved, in the future DCBI might be used as a neoadjuvant therapy making CRS-HIPEC with complete cytoreduction available for a larger number of patients.

We acknowledge the fact that this study has limitations. One limitation of this study is the small number of patients that will be included. Given the rarity of MPM, it is difficult to include large numbers of patients. However the sample size of this current study, should be sufficient to determine the feasibility and safety of adjuvant DCBI after CRS-HIPEC.

Another limitation of this study design is that it is not possible to determine radiological response to DCBI treatment. After debulking surgery, MPM will not be detectable on CAT scans. Therefore the response to DCBI treatment must be determined by assessing the immune response and overall clinical condition of each patient. Clinical effect of DCBI on overall survival can only be determined after a longer period of follow-up.

If DCBI is considered feasible as adjuvant treatment for MPM, a larger phase III clinical trial should be conducted to determine the effect on surgical and oncological outcome. Because MPM incidence in the Netherlands alone is very low, this clinical trial would have to be conducted internationally.
